## Abstract

**Background:**

Beyond causing significant morbidity and cost, musculoskeletal injuries (MSKI) are among the most common reasons for primary care visits. A validated injury risk assessment tool for MSKI is conspicuously absent from current care. While motion capture (MC) systems are the current gold standard for assessing human motion, their disadvantages include large size, non-portability, high cost, and limited spatial resolution. As an alternative we introduce the Micro Doppler Radar (MDR); in contrast with MC, it is small, portable, inexpensive, and has superior spatial resolution capabilities. While Phase 1 testing has confirmed that MDR can identify individuals at high risk for MSKI, Phase 2 testing is still needed. Our aims are to 1) Use MDR technology and MC to identify individuals at high-risk for MSKI 2) Evaluate whether MDR has diagnostic accuracy superior to MC 3) Develop MDR algorithms that enhance accuracy and enable automation.

**Methods and findings:**

A case control study will compare the movement patterns of 125 ACL reconstruction patients to 125 healthy controls. This study was reviewed and approved by the Pennsylvania State University Human Research Protection Program (HRPP) on May 18, 2022, and the IRB approval number is STUDY00020118. The ACL group is used as a model for a “high risk” population as up to 24% will have a repeat surgery within 2 years. An 8-camera Motion Analysis MC system with Cortex 8 software to collect MC data. Components for the radar technology will be purchased, assembled, and packaged. A micro-doppler signature projection algorithm will determine correct classification of ACL versus healthy control. Our previously tested algorithm for processing the MDR data will be used to identify the two groups. Discrimination, sensitivity and specificity will be calculated to compare the accuracy of MDR to MC in identifying the two groups.

**Conclusions:**

We describe the rationale and methodology of a case-control study using novel MDR technology to detect individuals at high-risk for MSKI. We expect this novel approach to exhibit superior accuracy than the current gold standard. Future translational studies will determine utility in the context of clinical primary care.

## Introduction

### Burden on military and athletes

Non-combat-related musculoskeletal injuries (MSKI) account for 80% of Service Members’ injuries, 60% of limited duty days, and 65% of days in which US Service Members are unable to deploy [1]. In 2014, MSKI accounted for $980 billion in healthcare dollars (5.76% of the annual Gross Domestic Product) [2]. MSKI are the greatest medical threat to Service Members’ health and readiness [3]. In addition, MSKIs result in increased military separation [4], exorbitant medical costs [5], and the development of chronic pain or long-term disability [6]. The impact of MSKI is not unique to the military; during the 2014–2015 National Basketball Association season, it was estimated that MSKI accounted for a loss of $344 million in player salaries [7]. During the 2019–2020 National Football League season, an estimated $521 million was spent on the treatment of MSKI [7]. Service Members and athletes represent younger and more physically fit subpopulations in which MSKI can substantially impair performance and have life-long consequences.

### Preventing musculoskeletal injuries

Primary MSKI risk reduction efforts have shown promise in decreasing MSKI rates; however, current screening methods still lack sufficient accuracy to identify injury risk [8]. The Center for the Intrepid and National Intrepid Center of Excellence have developed sophisticated assessment tools that are available, but require specialized facilities making their use dependent upon proximity to one of these centers. Comprehensive MSKI prediction modeling has potential to identify those at most risk; however, this requires extensive expertise and time, which limits its large-scale implementation [1, 3, 9]. Motion capture (MC) labs provide us with the most objective biomechanical parameters to accurately measure three-dimensional joint and body positions. These labs can be considered the gold standard for accessing those at risk for injury. Unfortunately, MC systems used for measuring whole body activities are large, expensive, have limited portability, and have spatial resolution capabilities limited to approximately what can be seen by the human eye [10].

An alternative approach to human motion analysis is the use of micro-Doppler radar (MDR), which is small, inexpensive, easily portable, and has been proven to distinguish subtle differences in movement patterns not detectable by the human eye [11, 12]. MDR has the ability to detect and evaluate movement at a scale that has never been visually distinguishable to date. In a previous study, MDR predicted when athletes had a 2 cm heel lift in their shoes 100% of the time, reflecting great accuracy in detecting subtle changes in movement patterns [12]. The radar’s accuracy in detecting micro-movements is the premise for using it to screen Service Members or athletes for the risk of MSKI. Identifying those with a high-risk of MSKI will allow limited preventative resources to be directed to the highest-risk population. Ultimately, this approach can decrease injury risk, incidence, and MSKI burden.

Relevant work on the use of MDR for gait analysis includes a study by Seifert et al., in which the researchers validated the feasibility of using Doppler radar to measure clinically relevant gait parameters [13]. The values of five spatiotemporal parameters extracted from radar measurements matched those obtained using MC. Additional data on kinematic parameters showed that measured radar velocities also agreed with the values obtained using MC, reflecting the feasibility of using MDR for gait analysis [13]. Another approach to gait analysis using MDR utilized trunk movement to estimate biomechanical gait parameters instead of the conventional leg-movement-based method [14]. Changes in leg positions relative to the radar make the extraction of ankle-echoes challenging, especially in practical conditions that do not involve walking on a treadmill [15–17]. Saho and colleagues demonstrated that the novel trunk method enables the estimation of the swing and stance times and that the inclusive trunk and leg-based method improves the accuracy of gait estimations [14]. These studies highlight the concept that MDR can be used in a manner similar to how motion capture labs have captured human mechanics previously, but with the advantages of MDR technology.

One high-risk group that has been studied extensively is patients with a history of an anterior cruciate ligament reconstruction (ACLR). Despite many years of research, patients with ACLR have a 6–24% chance of an ACL re-tear or a subsequent knee surgery on either side within 2 years of successful surgical intervention and post-surgical rehabilitation [18]. This could be due to movement deficits that persist beyond the typical rehabilitation period of nine months and are undetectable even by the trained eye [19]. Due to the known risk of re-injury, this population is one that needs further investigation beyond previous measures. Therefore, due to the accuracy of MDR, there may be an opportunity to utilize this technology for evaluating this high-risk population.

The previously completed work has shown that radar technology is an evolving and promising alternative to traditional motion analysis [11, 12]. The purpose of this paper is to describe a case-control study using novel methodology utilizing MDR to detect an at-risk group for MSKI. Our study aims to assess the feasibility of using MDR for identifying populations at risk of MSKI, to determine if MDR is superior to MC, and to advance MDR algorithms to enhance accuracy and prepare for automated data processing. Our hypothesis is that MDR will outperform MC in its ability to identify this high-risk population.

## Methods and materials

### Study design

This is a case-control study using MDR to compare the movement patterns of 125 adults with a history of ACLR to that of 125 healthy controls. This study was reviewed and approved by the Pennsylvania State University Human Research Protection Program (HRPP) on May 18, 2022, and the IRB approval number is STUDY00020118. Eligibility criteria can be found in Table 1.

**Table 1 pone.0292675.t001:** Inclusion and exclusion criteria.

	ACL Group	Control Group
**Inclusion Criteria**	Age 18–40	Age 18–40
	History of ACL reconstruction between 9–24 months before recruitment	No history of lower extremity surgery
	Medically cleared to resume normal activities	
**Exclusion Criteria**	Age <18 or >40	Age <18 or >40
	Pregnant or institutionalized	Pregnant or institutionalized
	Current neuromuscular disease	Current neuromuscular disease
	Inability to provide informed consent	Inability to provide informed consent
	Inability to perform study activities	Inability to perform study activities
	Inability to walk or jump without a limp	Inability to walk or jump without a limp
	History of cerebral vascular accident	History of cerebral vascular accident
	History of knee or hip replacement	History of lower extremity surgery

Recruitment will occur through a retrospective review of Electronic Health Records (EHR) to identify patients that have undergone ACLR within the past 9–24 months. These participants will be mailed a recruitment letter explaining the study and providing contact information for our study coordinator. Once the potential participant makes initial contact and shows interest, a link will be sent to their email with a REDCap database eligibility screener [20]. Additional recruitment will occur through a prospective review of the surgical schedule for future ACL surgery candidates or patients that have recently undergone surgery, but have not yet been cleared for full activity. These participants will be provided with study flyers by a member of their medical team, and if interested will contact the study coordinator for potential future recruitment. Participation of all recruited patients is conditional upon successful clearance for full activity by their medical team at the time of participation.

A control cohort will be recruited through study finder (institutional study database), and study recruitment flyers will be distributed throughout the participating institutions. All attempts will be made to match the cases and control by sex, body mass index (BMI), and age.

Interested individuals from both groups will be asked to complete a REDCap eligibility screener and will be directed to a summary explaining the research and electronic consent if found eligible. If consent is given, contact information and basic demographic data will be obtained through REDCap. A study member will then contact eligible and consented individuals to schedule their data collection time.

### Micro-Doppler radar system

The components needed for the assembly of the MDR will be purchased and packaged in a way that makes it easily transported and calibrated, based on previously published parameters for the radar system [11, 12]. The radar will be installed within a MC human performance lab so that the MDR data can be collected simultaneously with the MC data. The antennas for the radar system will be mounted at a height approximately 49 degrees to the participant. Because participants will be performing multiple activities at 0 degrees to the radar from varying distances, measurement distance will not be standardized. The radar itself will be set up outside of the data collection area so as to not disrupt the MC data collection with corresponding cables connected to the antennas and to the computer used for processing and storage of the pre-processed data.

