### Data collection

Upon arrival for their data collection session, the participant’s identification number will be checked, and they will fill out the Brief Pain Inventory Short Form, which will serve to identify any confounding pain effects on the testing protocol [21]. To mitigate the effects of possible fluctuations in pain perception, the pain survey will be administered immediately prior to the start of data collection.

Radar Micro-doppler signatures and biomechanical MC data will be simultaneously collected as participants perform a series of functional activities. Combining MC and MDR data collection presents unforeseen challenges. MC techniques are widely known and have developed a level of sophistication that allows for flexibility when positioning equipment in the data collection volume and selection of a marker set. Conversely, MDR is direction-specific in regard to the position of the antennae which in turn dictates the primary plane of action for the experimental task. Since body segment velocities for all three tasks in this experiment are primarily in the sagittal plane it is necessary to align the experimental apparatus with the MDR signal axis (0 deg from center of antennae). Once aligned, the challenge is to select a marker set where the experimental apparatus doesn’t obscure markers. The solution is to place extra tracking markers on the pelvis, forearms (wrists), and head. These markers can then be used as reference points in Visual 3D to create virtual markers, which are then used along with the actual markers to create the skeletal model.

The marker set used to produce the Visual 3D skeletal model (virtual and actual) consists of 34 markers which are used to calculate all joint and segment angles, and their time derivatives. Bilateral lower-body markers consist of medial and lateral toes (2nd metatarsal and little toe), heel (calcaneus), medial and lateral ankle (malleolus), and medial and lateral knee (Tibial condyles). Trunk markers consist of right and left (R&L) anterior superior iliac spine, R&L posterior superior iliac spine, R&L shoulder (acromion), lower neck (C7), mid-trunk (T8), and sternal notch. Bilateral arm markers consist of the medial and lateral elbow (humeral medial and lateral epicondyles) and the wrist (radial and ulnar styloid processes). Head markers consist of the left and right zygomatic arches directly anterior to the inter-aural axis and top of the head.

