Data from the ACLR and control groups will be collected by the MDR and MC systems simultaneously by a triggering system that matches the data collection on the time axis prior to the onset of movement. Participants will be asked to perform five trials of each of the following three tasks: Two-legged drop jumps (DJ2) from a low box (30cm), standing from a seated position, i.e., sit-to-stand (STS), and continuous gait on a treadmill. Participants will be asked to wear appropriate clothing and footwear for exercise training. Each task will be demonstrated by a research team member and participants will be given time to practice before data collection begins. Task order will be randomized, and all five trials of each task will be performed as a block. Participants will be given time to rest between practice and trial performances and in between trials during data collection to minimize fatigue effects. Any trial that deviates from the instructed methods will be evaluated and repeated before continuing. The three tasks will be completed in the frontal plane or 0 degrees with respect to the MDR.

The DJ2 task is usually performed without incident in clinically recovered patients during late or post-ACL reconstruction rehabilitation, while the STS and gait are typically applied earlier in the rehabilitation periods for patients who have not fully cleared rehabilitation. The three tasks selected are typical of ACLR rehabilitation, can be performed in any clinic, and cover a range of performance abilities.

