### Micro-Doppler signature processing

The process of extracting unique information from MDR begins with the construction of micro-Doppler signatures (MDS). There are various procedures for generating MDS that have been proclaimed as useful in helping discern between physical activities monitored by MDR. The most common approaches extract features from signatures constructed through time-frequency and cadence-frequency diagrams. After obtaining such signatures, activity classification often starts in the form of extracting features from the created signatures. One of the most prominent methods used when performing activity classification with MDR configurations is through the analysis of time-frequency representations of the received MDS. Time-frequency signatures implement the short-time Fourier transform (STFT) for analyzing MDS. After constructing signatures for each activity measured by the MDR, further processing is incorporated into the signatures for extracting unique information. A variety of methods have been employed in extracting features embedded in the signatures. There are two types of feature sets evaluated in this work. One type of feature is deemed “traditional,” being that they are handcrafted from the raw data. The other types of features are those extracted through machine learning techniques, such as dimensionality reduction. More specifically, we propose a dimensionality reduction technique that, as far as we have found, has yet to be implemented in the classification of human gait classification via MDR. We previously developed the micro-Doppler signature processing algorithm (mD-SPA) for processing the MDS to classify specific movement conditions [12]. We will apply the same algorithm to the three performance tasks discussed above in order to distinguish the ACLR group from the control group and determine the accuracy and predictability of the algorithm. This data will be used for comparison to the MC outcome data (outlined below). We will then calculate the sensitivity and specificity of MDR to the MC data to determine whether the participant is in the ACLR group or the control group.

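### Radar distance is explicitly left unstandardised for a reason that covers differences between tasks but not within a task, and the angle and plane wording needs reconciling

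*Protocol article*

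**What the plan says.** Four statements in the protocol article bear on the radar geometry.

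- *Micro-Doppler radar system*, on distance: "Because participants will be performing multiple activities at 0 degrees to the radar from varying distances, measurement distance will not be standardized".
- The same section, on the mounting: "The antennas for the radar system will be mounted at a height approximately 49 degrees to the participant". No height in metres, reference distance or reference point on the body is given, and the article does not say whether 49 degrees is an elevation.
- *Data collection*, on the instrument: "MDR is direction-specific in regard to the position of the antennae which in turn dictates the primary plane of action for the experimental task". It goes on to say that "body segment velocities for all three tasks in this experiment are primarily in the sagittal plane", so the apparatus has to be lined up with the radar's signal axis at 0 degrees.
- Later in *Data collection*: "The three tasks will be completed in the frontal plane or 0 degrees with respect to the MDR".

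The signatures recorded this way are what the classifier uses. Under *Micro-Doppler signature processing*: "We will apply the same algorithm to the three performance tasks discussed above in order to distinguish the ACLR group from the control group".

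**The concern.** A Doppler radar registers the part of a velocity that lies along its line of sight. When the line of sight is oblique, moving the participant nearer or further changes that part even if the movement is identical. The article accepts that the radar depends on direction. It describes motion capture as tolerant of where equipment is placed. Uncontrolled position would therefore fall mainly on the radar, the system the study hopes to show is superior.

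The study looks for differences too subtle to see. Artefacts of a few percent in the recorded velocities are therefore worth removing when that is almost free. A signature recorded at an unlogged distance would be hard to correct afterwards.

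**Working it through.** The article gives no figure for this effect, so there is nothing to reproduce. The check has two parts.

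**1. Geometry**

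Inputs:
- Angle of 49 degrees, from *Micro-Doppler radar system*. Assumption: it is the elevation at some reference distance d0.
- Antenna height above the tracked body part. Assumption: fixed, so h = d0 × tan 49° = 1.150 × d0.
- Distance d = f × d0. No distance is given, so the work is in ratios. The values of f are illustrative.

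Formulas:
- Elevation: θ = arctan(tan 49° / f)
- Share of horizontal (toward–away) velocity seen by the radar: cos θ. Reference value: cos 49° = 0.656.
- Share of vertical velocity seen: sin θ. Reference value: sin 49° = 0.755.

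At f = 1.1: 1.150/1.1 = 1.046, so θ = 46.3°. Horizontal: 0.691/0.656 = 1.053. Vertical: 0.723/0.755 = 0.958.

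At f = 0.9: 1.150/0.9 = 1.278, so θ = 52.0°. Horizontal: 0.616/0.656 = 0.939. Vertical: 0.788/0.755 = 1.044.

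| Distance relative to reference | Elevation | Horizontal, relative | Vertical, relative |
|---|---|---|---|
| 0.75 | 56.9° | 0.83 | 1.11 |
| 0.9 | 52.0° | 0.94 | 1.04 |
| 1.0 | 49.0° | 1.00 | 1.00 |
| 1.1 | 46.3° | 1.05 | 0.96 |
| 1.25 | 42.6° | 1.12 | 0.90 |
| 1.5 | 37.5° | 1.21 | 0.81 |

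A 10% change in distance either way therefore moves the components by about 4 to 6%. The elevation column shows that one mounting height holds about 49 degrees only near the reference distance. At 1.5 times that distance it is 37.5 degrees.

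Two other geometries give a different answer. If the height is re-set to hold 49 degrees at each distance, the shares do not change and only echo strength does. The same is true if the radar is level with the moving segment and on axis.

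**2. Plane wording**

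| Place | Plane named | Alignment named |
|---|---|---|
| *Micro-Doppler radar system* | none | 0 degrees |
| *Data collection*, marker and alignment paragraph | sagittal | 0 degrees, on the signal axis |
| *Data collection*, task paragraph | frontal | 0 degrees |

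The alignment is the same in all three places. Only the name of the plane differs, for the same three tasks.

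**The case against.** The strongest reply is that the natural reading of the distance sentence is variation between tasks only. Everyone in both groups performs the same three tasks, and those tasks tie the participant to a box, a seat or a treadmill. The drop jump is to be straight up. Distances that differ by task but are shared by cases and controls would not bias the classification. This reply largely stands as a reading of intent. It does not rescue the sentence, which declares distance unstandardised without limiting that to differences between tasks.

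A second reply is that the fixed antenna height is not in the text. The article gives an approximate angle, and the height might be adjusted to keep it. That also stands, and it makes the 4 to 6% conditional. It leaves the article needing to say whether height or angle is held constant.

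A third reply is that floor positions and logs belong in a laboratory manual or the full protocol. That would answer a complaint about missing detail. Here the article makes a positive statement that distance will not be standardised.

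Three stronger readings are tempting and are not supported:

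- A reader might infer from sagittal versus frontal that a participant could be set up side-on. All three statements give 0 degrees, and the requirement to align sagittal movement with the signal axis excludes standing side-on. The word frontal may simply mean facing the radar.
- A reader might compare the same jump at one distance and at twice that distance and infer a very large loss of Doppler shift. Nothing suggests that one task is done at two such distances.
- A reader might infer that the classifier will learn the set-up instead of the movement. That needs set-up to differ by group, through drift, operators or testing periods. Cases and controls are recruited through different channels, but nothing says that their set-up differs.

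**Conclusion.** The point holds as a matter of avoidable noise and unclear specification. Three things need correcting: distance within a task is left free on a reason that does not cover it; one mounting height cannot give about 49 degrees at every distance; and *Data collection* names two planes for the same tasks.

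The size is about 4 to 6% in the line-of-sight velocity components per 10% change in distance. It rests on 49 degrees being an elevation, on a fixed antenna height, and on distance actually varying within a task. None of these is confirmed by the text. The documents give no way to turn the figure into lost sensitivity or specificity.

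Variation unrelated to group would lower radar accuracy and so work against the study's own hypothesis. Bias in the comparison with motion capture is possible only if set-up differs between cases and controls, and it is not shown. The change is worth making because it is cheap, and the point is a modest one.

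**What to change.** In *Micro-Doppler radar system*, replace the distance sentence with a statement that each task (box, seat, treadmill) has one fixed, marked floor position and heading. State one fixed antenna height and tilt. Both should be the same for all participants, with the measured distance logged.

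Say which angle is elevation and which is azimuth. With a fixed height and different distances by task, also say for which position the 49 degrees holds, or give the angle for each task.

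In *Data collection*, reconcile the sagittal and frontal wording, separating the plane of movement from the direction in which the participant faces.

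The cost is floor marking, one log field and a few sentences. No extra participants or procedures are needed, and the scheduling of cases and controls need not change.
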